### Power Analysis

Because the nature of aim 2 was primarily to examine feasibility, we aimed only to observe large effects (*f*=.40) with a modest degree of power (β=.80). The results of the power analysis based on rmANOVA with α=.05 indicate that the proposed sample size (n=18 per condition) is adequate for proposed analysis (minimum n=16). Because intervention efficacy is an exploratory aim in this pilot test, we are not attempting to power the analyses for aim 3.

### Oversight, Monitoring, and Stopping Rules

Each week, research staff will check in with CM participants via Questionnaire of Smoking Urges item and TLFB. Research staff will also assess CM participants for AEs and serious adverse events (SAEs) weekly and report all AEs to the PI per local institutional review board (IRB) guidelines and in accordance with ClinicalTrials.gov standards [55]. All participants will be assessed for AEs at week 0 and week 6. For any participants who wish to withdraw during the study, reasons for withdrawal will be documented, if available. Participants who have lost contact after an expected contact or visit for at least 1 month will be withdrawn from the study. Exceptions may be made after discussions with the PI, in consultation with the Data Safety Monitoring Board (DSMB), and in consistency with the regulations of IRB.

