## Introduction

### Background

Major surgery is common among veterans, and smoking is the most significant modifiable risk factor for perioperative morbidity and mortality [1]. The Veterans Affairs (VA) Health Care System performs over 600,000 major elective surgeries annually, including general, thoracic, vascular, urologic, spinal, and other orthopedic procedures [2]. Unfortunately, smoking prevalence among patients undergoing major elective surgery is high, ranging between 22.3% and 43.0%, and is highest among uninsured patients (36.3%) and Medicaid recipients (43.0%) [3]. Reducing complications and death after major elective surgery is a top priority for both veterans [1] and the general population [3]. Smoking-related postoperative risks include pneumonia, prolonged intubation, myocardial infarction, and stroke [4-6]; infections, sepsis, and poor wound healing [4-9]; and repeat procedures [4-9]. Active smoking status at the time of surgery is the single greatest risk factor for complications, reoperation, and death [4-9]. The relative risk (RR) of death in 30 days following major surgery is 1.5 times higher in smokers than in nonsmokers [8,9]. Accordingly, the American College of Surgeons recommends that smoking cessation counseling be offered during all nonemergent consultations [9].

The preoperative period offers a critical opportunity to promote behavior change [3,10,11]. A systematic review of clinical trials found that intensive perioperative smoking cessation programs, with sessions before and after surgery, increased the likelihood of postoperative abstinence in both the short term (odds ratio 2.41, 95% CI 1.95-2.98) and the long term (odds ratio 1.64, 95% CI 1.23-2.20) [10]. Another systematic review and meta-analysis examining rehabilitation interventions for behavioral change concluded that participation in 4-week behavioral interventions before surgery was associated with higher odds of cessation (RR 2.9, 95% CI 1.7-4.8; *I*^2^=84%) and sustained abstinence at 12 months post surgery (RR 1.74, 95% CI 1.20-2.55; *I*^2^=43%) [11]. Taken together, intensive smoking cessation interventions before and after surgery can improve short-term and long-term quit rates.

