## Methods

### Participants and Eligibility

Inclusion criteria are as follows: (1) veterans enrolled in the San Francisco VA Health Care System (SFVAHCS), (2) those recommended or scheduled for major elective surgery within the next 6 months (eg, general, spinal, thoracic, vascular, urological, gynecological, orthopedic, or other surgeries), (3) those currently (ie, past 30 d) smoking a minimum average of 1 cigarette per day, (4) those having daily access to a personal smartphone device and Wi-Fi, and (5) those open to receiving smoking-cessation interventions. Veterans followed by primary care who are referred to external institutions for major elective surgery will also be eligible.

Exclusion criteria will be evaluated through medical record review and clinical assessment: (1) psychotic, bipolar, or neurocognitive disorders or other psychiatric or medical conditions judged to be unstable in the past 30 days; (2) untreated, current, active problem gambling, as assessed by a medical record diagnosis or a Problem Gambling Severity Index (PGSI) score ≥8; (3) enrollment in end-of-life or palliative care; (4) surgery with a clinical indication for cancer; (5) unable to meet time commitment; (6) currently pregnant or planning to become pregnant during the study [21]; (7) a suicide attempt, or suicidal ideation with intent, within 30 days prior to enrollment; and (8) concurrent participation in another tobacco cessation trial.

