### Recruitment and Overall Study Schedule

Participants will be recruited through (1) data queries of VA electronic health record data available through the VA Corporate Data Warehouse and (2) direct recruitment. Data queries will identify patients with an upcoming major elective surgical procedure from a predefined list. We will then identify individuals with documentation of current smoking, using an established approach via the Corporate Data Warehouse national VA database with codes, or “health factors.”

Partners in surgical subspecialties will assist with recruitment through referrals. Direct recruitment will allow the team to recruit participants with a stated interest in tobacco cessation and facilitate targeted recruitment in clinics that serve women and members of underrepresented minority groups. If recruitment rates decrease to below 2 participants per month, we will expand the eligibility criteria from major surgeries to include less invasive eye surgeries and podiatric surgeries.

The protocol eligibility criteria were developed to include participants up to 6 months prior to surgery to improve generalizability after extensive discussions with colleagues in surgery. Surgical colleagues described that some elective major surgeries (eg, some orthopedic, vascular, and neurosurgeries) may not be scheduled for months until successful smoking cessation has occurred, given the risks of cigarette smoking and impaired wound healing with some procedures. Therefore, to be as inclusive as possible to a range of participants awaiting scheduling for elective major surgery, the eligibility criteria include participants who smoke up to 6 months prior to surgery. The preoperative period varies by participant and is being tracked in this pilot study.

Once a veteran participant is recruited, we will follow the study timeline as delineated in Table 1. This schedule of enrollment, interventions, and assessments adheres to the latest SPIRIT (Standard Protocol Items: Recommendations for Interventional Trials) guidelines for reporting (Checklist 1) [35].

**Table 1. T1:** Schedule of enrollment, interventions, and assessments.

	Trial period							
	Enrollment		Postrandomization					Closeout
	Screening and baseline		Intervention phase					Follow-up
Time point (wk)	Week −4	Week 0^a^	Week 1	Week 2	Week 3	Week 4	Week 5	Week 6^a^
Time window (d)^b^	30	7±14	7	7	7	7	7	7+14
Enrollment								
Eligibility screen	✓							
Informed consent	✓							

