### Other Data Documentations

A review of the VA medical record will be completed at baseline and posttreatment by staff, assessing medical conditions and treatment. Surgical complications will also be documented as adverse events (AEs). There are no restrictions on concomitant medical and mental health treatment. Concomitant medical and mental health treatment will be documented for all participants to track participants’ engagement in other interventions, and TAU participants will have their number of sessions in TAU interventions tracked.

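### Adverse events are solicited weekly in CM but only at weeks 0 and 6 in TAU, so any by-arm count, especially of mild or transient events, would tend to run high in CM

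*Protocol article*

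**What the plan says.** Two sentences in the protocol article, under Oversight, Monitoring, and Stopping Rules, set the AE schedule. For the intervention arm: "Research staff will also assess CM participants for AEs and serious adverse events (SAEs) weekly". For everyone: "All participants will be assessed for AEs at week 0 and week 6". No weekly AE enquiry is stated for TAU. Under Randomization and Blinding, the article says that nobody on the study team is blinded.

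A second source of events covers both arms. Under Other Data Documentations: "A review of the VA medical record will be completed at baseline and posttreatment by staff, assessing medical conditions and treatment". Table 1 also marks the record review at the week 6 follow-up, without distinguishing the arms.

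The same section adds: "Surgical complications will also be documented as adverse events (AEs"). On the timing of surgery, eligibility covers "those recommended or scheduled for major elective surgery within the next 6 months". The recruitment section says that some procedures "may not be scheduled for months until successful smoking cessation has occurred". It also says: "The preoperative period varies by participant and is being tracked in this pilot study".

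The DSMB monitors AEs among other things, results are to follow CONSORT, and findings are to be posted on ClinicalTrials.gov. The Data Analytic Plan describes no AE analysis and no AE table by arm.

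**The concern.** How many events are recorded depends on how often people are asked. A headache, a poor night's sleep or a few days of nausea is more likely to be mentioned to someone asking that week than to someone asking once, up to six weeks later. Both arms are offered nicotine replacement, bupropion or varenicline, so minor medication-related complaints can arise in either arm, yet they are asked about weekly only in CM. Because the staff who ask know the allocation, blinding offers no protection.

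At stake is the reading of any AE count set out by arm. With 18 participants per arm, a few extra recorded events change the impression. The DSMB can recommend that the study continue, be modified or be terminated, so an excess created by the schedule should not reach it unlabelled.

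**Working it through.** The article states no AE rate, safety margin or safety power, so there is no figure to reproduce. The check has three parts.

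**1. Enquiries per arm (from the article).**
- CM: week 0 + weeks 1 to 5 + week 6 = 1 + 5 + 1 = 7, of which 6 follow randomization.
- TAU: week 0 + week 6 = 2, of which 1 follows randomization.

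The week 0 enquiry precedes the intervention, so the relevant contrast is 6 against 1.

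**2. What this could do to counts (all rates assumed).** Take the same true AE rate in both arms, with events spread evenly over weeks 1 to 6. An event is reported with probability 0.9 if asked about in the same week, and that probability is multiplied by r for each week that passes before the enquiry.
- CM detection: 0.9.
- TAU detection: 0.9 × (1 + r + r² + r³ + r⁴ + r⁵)/6.

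| r | CM | TAU | CM:TAU |
|---|---|---|---|
| 1.0 | 0.900 | 0.900 | 1.00 |
| 0.9 | 0.900 | 0.703 | 1.28 |
| 0.8 | 0.900 | 0.553 | 1.63 |
| 0.7 | 0.900 | 0.441 | 2.04 |

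In participants, at r = 0.8 and a true mean of 1 AE per person (Poisson), the expected number with at least one recorded AE is:
- CM: 18 × (1 − e^(−0.9)) = 10.7
- TAU: 18 × (1 − e^(−0.553)) = 7.7

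At 0.5 AE per person the figures are 6.5 and 4.4.

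Now let the record review catch a fraction c of the events missed at interview, equally in both arms. The ratio is [1 − (1 − c)(0.1)] / [1 − (1 − c)(0.447)]:
- c = 0: 1.63
- c = 0.5: 0.950/0.777 = 1.22
- c = 0.8: 0.980/0.911 = 1.08
- c = 1: 1.00

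If the comparison uses only sources applied identically in both arms, the ratio in this model is 1.00 by construction.

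**3. Surgical complications (all rates assumed).** The expected count is 18 × P(surgery before follow-up) × P(complication | surgery). Suppose 30% of CM and 15% of TAU are operated on in the window, with a 20% complication risk in TAU (0.54 expected).
- CM risk 20%: 18 × 0.30 × 0.20 = 1.08 against 0.54.
- CM risk 10%: 18 × 0.30 × 0.10 = 0.54 against 0.54.
- CM risk 8%: 18 × 0.30 × 0.08 = 0.43 against 0.54.

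The difference can go either way, and the article gives none of these inputs.

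**The case against.** Four objections deserve an answer.

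*No by-arm safety table is described.* This is correct. A reader might infer that a planned table is biased. The article names CONSORT, ClinicalTrials.gov and DSMB review but sets out no AE comparison. Tabulation by arm is the ordinary expectation for a two-arm trial, but it remains an inference, so the point has to be conditional.

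*Tabulation belongs in an analysis plan that is not shown.* This stands for table layout. It does not remove the point, because the article itself fixes the collection schedule, and the unequal schedule is what creates the problem.

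*Both arms have the week 6 enquiry and the record review.* This also stands. SAEs and surgical complications depend much less on weekly contact than minor events do. The protection is incomplete: a chart review of conditions and treatment is unlikely to pick up brief, self-managed complaints, and participants referred to outside institutions for surgery are eligible, so the VA record may miss some events.

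*Quitting can bring surgery forward, so complications would be counted against CM.* This is the tempting stronger reading, and the documents do not support it as a bias. Earlier surgery after quitting would be an effect of randomized treatment, and counting complications per randomized participant agrees with the stated intent-to-treat approach. The direction is also unknown. The Background says "Active smoking status at the time of surgery is the single greatest risk factor for complications, reoperation, and death", so an effective intervention should lower risk at operation. The share operated on before follow-up is not given. Using only operated participants as the denominator would condition on an event after randomization that treatment may affect, so it can serve only as description.

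**Conclusion.** The point holds for ascertainment. The article fixes six post-randomization AE enquiries in CM against one in TAU, unblinded, so raw by-arm counts of AEs would tend to be inflated in CM, above all for mild or transient ones. The asymmetry is plain from the text, and its direction for such events is well founded. Its size is not known: the ratios of 1.28 to 2.04 rest on assumed detection and recall, ignore the record review, and fall towards 1 as the review captures more. A reader should not take a twofold excess as established.

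Nothing is concluded about whether surgical complications would favour either arm. This is a 36-person feasibility pilot with no safety endpoint among its primary outcomes. The point therefore concerns how AE data may be read and does not threaten the main aims. It is still worth settling before the preliminary analysis expected by August 2027, and for DSMB reports before then.

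**What to change.** State the following rule in the protocol or analysis plan:

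1. Any between-arm AE comparison, including in DSMB reports, uses only sources common to both arms: the week 6 enquiry and the posttreatment record review. For the two to match, the week 6 enquiry should use the same questions and cover the whole period since week 0 in both arms.
2. Events found only at weekly CM contacts are listed in full, separately, and labelled as CM-only ascertainment. This requires recording the source of each event.
3. Surgical complications are shown apart from other AEs, per randomized participant. The number operated on before follow-up and the days observed after surgery are given by arm as description only. No claim is made about the direction of any difference.

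The cost is a reporting rule, table shells and a source field, with no new visits; the preoperative period is already being tracked. The downside is fewer CM events in the comparative table, though none is lost from the listings. A residual limitation should be stated: weekly questioning may sharpen CM participants' recall at week 6, so the common sources reduce the imbalance but may not remove it.

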### CM Training, Supervision, and Fidelity Monitoring

Study investigators, who have demonstrated competency in national VA CM training rollouts [34], will train therapists and staff. The CM feedback sessions will be audio-recorded for the purpose of weekly supervision and fidelity monitoring. Approximately 10% of recordings will be randomly selected to rate adherence using the modified CM Competence Scale for Reinforcing Abstinence [25], a validated 12-item scale that measures adherence to CM principles in bioverification, assessing the salience of reward, praising abstinence, assessing cravings or urges, and empathy. All data collected will be entered into and stored in an encrypted Excel file, an Access database, and VA REDCap behind the VA secure firewall. The PI and the lab manager will review and perform data fidelity checks at least once a month.

### Composition of the Data Monitoring Committee

The DSMB is a group of clinical researchers who are not part of the investigative team. The DSMB will meet semiannually to review data reports prepared by the PI regarding the progress of the study and will monitor enrollment, retention, outcomes, AEs, and other issues related to patient safety. The DSMB will make recommendations to the PI as to whether the study should continue, be modified, or be terminated.

### AE Reporting and Harms

Research staff will document all AEs and SAEs and review them with the PI as described. All AEs and SAEs will be followed until resolution or until they are deemed to be chronic by the PI or until the participant is lost to follow-up.

### Ethical Considerations

The study was conducted in accordance with the Declaration of Helsinki and was approved by the IRB of the University of California, San Francisco (UCSF; IRB number 24‐41632; date of approval: September 16, 2024) and SFVAHCS Research Administration (reference number HERE-0017). A recent annual IRB continuing review was performed and approved on August 22, 2025. Any changes in the study protocol will be submitted to the UCSF IRB for review and approval, and the approved changes will be updated accordingly on ClinicalTrials.gov and submitted to DSMB.

Veterans will be mailed or emailed IRB-approved 2-week opt-out letters, be directly referred by clinicians, or directly refer themselves. Interested veterans will initially be screened for eligibility in person or over the phone using a brief screening checklist. Prospective participants will then meet with a team member to complete written informed consent in person at the San Francisco VA Medical Center or virtually via DocuSign, Inc, and proceed with screening. Study ID numbers will be assigned to each participant to protect their data privacy.

## Results

### Status of This Study

This pilot trial has been funded since July 2024, and a 1-year no-cost extension has been granted through June 2027. The recruitment and data collection started in December 2025. The first participant consented on December 12, 2026. As of May 2026, 18 participants have been enrolled and randomized in this pilot trial so far. The enrollment of the last participant is expected to be in March 2027 to reach a target of 36 enrolled participants, and the data collection is expected to be completed by April 2027. There will be no interim data analysis, but preliminary analysis is expected to be completed by August 2027, and all data analyses are expected to be completed by the end of 2027.

### Dissemination and Data Sharing Plan

The results will be disseminated through abstracts, presentations, and manuscript submissions. Findings will be published on ClinicalTrials.gov at the end of the study. The results will be shared in collaboration with the project community advisory panel, a multidisciplinary group of VA policymakers, and clinicians with subject matter expertise in TUD, behavioral treatment of SUD, surgery, and anesthesia. Analytical codes and the established mCM manual will be shared on the Open Science Framework. Study data will not be shared with the public but will be processed upon request in accordance with the VA data privacy policy.

## Discussion

Given the critical link between cigarette smoking and surgical outcomes and the high prevalence of smoking in those seeking major elective surgeries, we aim to adapt and test a brief, rigorous, CM smoking-cessation protocol in a perioperative setting for veterans undergoing major elective surgeries. We aim to extend established CM protocols and remain consistent with gold-standard CM practices using remote bioverification, a fixed incentive structure, and consulting with subject matter experts in the development of the protocol.

Potential barriers to success may include issues such as technology or internet issues, a high frequency of bioverification, an inability to bioverify for the use of electronic cigarettes and noncigarette tobacco products, and the heterogeneity of the surgical population [48,56]. To mitigate selection bias and attrition, our strategies will include 1 week of training and practice, ordering digital-support consults as needed and video conferencing with staff to obtain CO readings if needed. Additionally, the short half-life of CO poses a challenge to identifying a feasible, outpatient bioverification schedule that confirms daily smoking abstinence. VA protocols for smoking cessation were designed for residential treatment settings, with daily CO monitoring conducted on-site. One challenge of including participants who use smokeless tobacco, e-cigarettes, and other tobacco products is that we cannot bioverify abstinence from these products using CO monitoring. We will focus on smoking cessation bioverification and collect data pertaining to the cessation of other nicotine and tobacco products through TLFB. The CO abstinence verification plan implemented in this CM protocol aims to strike a balance between feasibility and scalability in outpatient settings and specificity in identifying bioverified abstinence from combustible cigarettes only. Our group operationalized the standard definition of smoking abstinence as self-report verified by CO≤6 ppm, as is recommended by SRNT consensus guidelines [47]. The 5-days-per-week, once-per-day CO video upload schedule includes same-day, rapid clinician feedback, which is a critical component of CM [25]. The protocol allows for optional weekend and holiday videos as well, but those videos cannot be reviewed and addressed on the same day due to outpatient staffing. The short half-life of CO and the challenge of demonstrating durable abstinence is an inherent limitation of any smoking cessation CM protocol in which nicotine replacement products are offered to be prescribed (preventing the use of cotinine testing among those prescribed NRT). Once-daily CO monitoring has been considered adequate for most smoking cessation protocols, including those in VA residential treatment programs.

Finally, surgical procedures may vary in terms of requiring vs recommending smoking abstinence preoperatively. However, for this pilot study, the type of surgery will be inclusive to facilitate recruitment and generalizability, and we will use systematic data queries to minimize selection bias in recruitment.

This project will elucidate the feasibility and efficacy of an mCM-for-smoking-cessation outpatient protocol in veterans undergoing major elective surgery. Given the negative impact of smoking on surgical outcomes and the unique window of opportunity for intensive, focused intervention afforded perioperatively, we expect this program to have high potential utility to improve surgical outcomes and reduce the burden of smoking-related disease.
